#### Surgery

Patients randomised to surgery will immediately be placed on the waiting list for surgery, with the expectation that surgery will be performed within 4 months. This reflects the average current surgical waiting time in the NHS. The surgical group to which the patient has been allocated will be concealed from the surgical team and revealed only on the day of planned surgery.

#### Active monitoring with specialist reassessment

Patients randomised to the AMSR group will receive a letter stating that a specialist reassessment appointment will be scheduled for a date 3 months hence. The reassessment will identify any patients who require adjustment to their management.

#### Informed consent

Patients will be asked to opt in to the study before receiving further information and asked to attend a baseline appointment. The opt-in form does not obligate the patient to participate in the study, but it will allow members of the CSAW Study team (both locally and centrally) to contact them further. Full consent will be obtained during the baseline visit by the participating surgeon or by qualified local centre study staff. The Principal Investigator at this centre will have overall responsibility for consenting patients, but can delegate the task to reliable members of the study team. Such delegation will be recorded on a Task and Responsibilities Log during centre initiation. Informed consent will be obtained according to Good Clinical Practice guidelines. Patients will be given sufficient time to accept or decline involvement. They will be free to withdraw from the study at any time without affecting their routine care.

Patients who complete the opt-in form but decline to be randomised may also be contacted in relation to the CSAW Cohort Study and the QRI. Satellite studies associated with the CSAW Study will have their own informed consent process. These are detailed later in the protocol.

#### Qualitative recruitment investigation

To characterise and understand the success or failure of the CSAW Study recruitment process, the QRI findings will be reviewed. These data will inform changes to aspects of the design, conduct and organisation of the trial and future surgical trials and to provide training which could potentially lead to improvements in recruitment. All findings and any suggested changes are fed back first to the CI and RCT staff involved in the TMG. Further details of the CSAW Study QRI process can be found in Additional file 1.

#### Study assessments

Participating surgeons will be asked to coordinate their waiting lists to ensure the CSAW Study patients are called for surgery in accordance with the study protocol. Prestudy questionnaires have been designed to screen sites for their ability to conform. Ideally, patients will complete their baseline assessments as close to the randomised treatment as possible (within 4 months). However, owing to the expected variability inside the 4-month window, and in the event of the unfortunate (but quite possible) breach of this 4-month window in a minority of patients, contingency measures have been incorporated to maintain design integrity. In the event that surgery cannot be performed within 4 months of randomisation, the same questions and assessments completed at baseline will be repeated. This assessment will be performed within the 2 weeks leading up to the patient’s operation (either on the day of surgery or at the preoperative assessment appointment). This will highlight any changes in the patient’s shoulder pain and function.

Follow-up measurements will be conducted postrandomisation. All patients will be followed up at 6 and 12 months postrandomisation, with patients in the AMSR arm having their specialist reassessment at 3 months postrandomisation. To capture the full effect of the intervention, patients who are on surgical waiting lists for longer than 4 months will have an additional 12-month posttreatment assessment. Each follow-up point will involve a clinical assessment, so patients will be asked to attend hospital for an appointment. Clinical assessments and questionnaires can be completed during these visits. The attendance of patients for an appointment will also ensure that the patients allocated to the nonoperative arm receive the specialist reassessment.

#### Compliance and loss to follow-up

We anticipate that 90% of patients will accept their allocated treatment (no immediate crossover), and therefore we have accounted for a dropout rate of 15% from the entire study over time. These estimates are based on assessments of our UKUFF study data. Compliance and withdrawals will be monitored as the CSAW Study progresses. The end of the study is set as the date of the last follow-up visit of the last patient.

### Study interventions

Patients randomised to surgery will remain unaware of which procedure they have undergone (ASAD or AO). The CSAW Study surgical procedures will mirror each other. Both operations will be performed through two arthroscopic keyholes. Standardised postoperative care and rehabilitation will be applied for both groups (ASAD and AO). If any unexpected pathology is encountered, such as full-thickness rotator cuff tear, frozen shoulder or arthritis, the patient will receive treatment for this pathology while under the same anaesthetic. In such a case, the participant will continue to be followed up for the study. Preoperative imaging of the shoulder (ultrasound and MRI scan) is known not to be fully accurate (inaccuracy rate of approximately 5%), and it is usual practice to advise patients of this. As a consequence, consent is routinely obtained in surgical settings for any additional treatment that may be required if an unexpected pathology or problem is encountered. The CSAW Study protocol dictates that when consent for the surgery is taken, surgeons will inform patients that they will be consented for shoulder arthroscopy, plus or minus an arthroscopic subacromial decompression, plus or minus a rotator cuff repair. This will ensure that patients are informed of the risks of surgery and potential eventualities. Further details of the individual interventions are given below.

#### Arthroscopy only

The AO arm is the surgical comparison group. The procedure is performed with the patient under general anaesthesia. Patients will undergo a routine investigational arthroscopy of the joint and rotator cuff tendon. The operation will be performed in exactly the same manner as that in the ASAD group. Investigational arthroscopy has all the same essential operative components (and risks) of ASAD, but it does not involve surgical removal of any spurs or bursal tissue or release of the coracohumeral ligament. The procedure does involve the GHJ and the subacromial bursa being inspected and irrigated. Structures can be assessed for integrity and damage. The rotator cuff can be assessed for evidence of full-thickness tears. The synovium and lining of the shoulder can be assessed for evidence of capsulitis, arthritis or frozen shoulder. The time spent in the operating theatre will be similar to that for the ASAD group. These measures provide the AO group with the characteristics necessary to provide a reasonable comparison and account for the placebo effects of surgery.

#### Active monitoring with specialist reassessment

Patients will be advised that they will undergo active monitoring. They will attend a reassessment appointment 3 months after entering the study. At that appointment, they will be asked to complete questionnaires related to their shoulder pain and undergo a clinical assessment of the shoulder, including a record of any further conservative treatment. If, at the end of the 6-month assessment period, patients remain sufficiently symptomatic to require further intervention (based on clinical judgement), then additional treatment options will be discussed. It should be noted that the inclusion criteria state that all patients will have undergone conservative treatment (including physiotherapy and injection) before entering the trial. From an ethical standpoint, it is emphasised that it is quite within normal practice to have a period of active monitoring.

### Blinding

Blinding is performed for both patients and postintervention assessors in the surgical groups. For the AMSR group, blinding of the postintervention assessors only is appropriate and therefore will be applied. There will be a nominated unblinded person at each participating site. This person will be the main contact person for the patient and for the central study team in Oxford. Patients will be encouraged to contact this person for queries, if they have any complications and if they wish to pursue a different treatment option.

### Safety

There are no anticipated safety issues with the CSAW Study. Data on complications will be recorded as outcomes, and their severity and frequency will be assessed. Standard NRES safety reporting measures will be adhered to.

### CSAW Study complications

Expected complications in the CSAW Study are as follows:Frozen shoulderJoint and/or soft tissue infectionFurther shoulder surgery

Local study teams that identify any complications will notify the CSAW Study office in Oxford. To maintain blinding, further information about the complications will be collected from the patients or the unblinded person at the corresponding site. The CSAW Study team in Oxford will coordinate collection of these data. Complications will be deemed serious if they meet the criteria listed below.

### Definition of serious adverse events

A serious adverse event (SAE) is any untoward medical occurrence thatResults in deathIs life-threatening*Note*: The term *life-threatening* in the definition of *serious* refers to an event in which the participant was at risk of death at the time of the event; it does not refer to an event which hypothetically might have caused death if it were more severe.Requires inpatient hospitalisation or prolongation of existing hospitalisationResults in persistent or significant disability and/or incapacity or is a congenital anomaly/birth defectOther important medical events

*Other events* refers to any event that may not result in death, is not life-threatening or does not require hospitalisation, but may be considered a serious adverse event when, based upon appropriate medical judgment, the event may jeopardise the participant’s health and may require medical or surgical intervention to prevent one of the outcomes listed above.

### Reporting procedures for unexpected serious adverse events

An unexpected serious adverse event (USAE) should be reported to the REC that gave a favourable opinion of the study when, in the opinion of the CI, the event is:Related (that is, it resulted from administration of any of the research procedures)‘Unexpected (that is, the type of event is not listed in the protocol as an expected occurrence)

Reports of related SAEs and USAEs should be submitted within 15 days of the CI’s becoming aware of the event, using the NRES Report of Serious Adverse Event Form (available from: http://www.dt-toolkit.ac.uk/resourceindex/all.cfm).

### Statistics and analysis

#### Target sample size

A total sample size of 300 patients is planned. For a balanced three-group trial, this means that approximately 100 patients will be recruited per allocation group (ASAD, AO and AMSR).

#### Sample size calculation

The sample size calculation is based on the primary outcome measure, the OSS at 6 months postrandomisation.

Currently, there is no established minimal clinically important difference (MCID) for the OSS. In the absence of this, an approximation to the MCID can be based upon the change in the score between pre- and posttreatment. One-half of the standard deviation (SD) of this change could be viewed as an important change. In previous studies, the SD of the change in OSS has been estimated to be 9.0, giving a target difference of 4.5.

Using a two-sided *t*-test, 90% power to detect a difference in OSS of 4.5 (SD 9.0), with a two-sided 5% level of significance (α), a sample size of 85 participants is needed in each group. Accounting for dropouts and loss to follow-up of up to 15%, 100 participants are required in each group. Therefore, we aim to recruit a total of 300 participants (100 per treatment group) into the CSAW RCT. No adjustment was made for multiple comparisons.

#### Recruitment rate and access to the National Health Service

A total of 300 participants need to be recruited over 36 months. For 14 centres, this would mean an average recruitment of 21 to 22 patients per centre over 3 years (or approximately 7 patients per centre per year). As one-third (approximately 7) of these will be allocated to the AMSR group, the number of patients recruited for a surgical procedure will be around 14. When considering the availability of operating theatre time for this procedure, 14 operations are considered entirely manageable within 3 years. The addition of any further centres to the trial would decrease the average number of operations per centre required for the trial.

#### Analysis of endpoints

##### General considerations

The statistical analysis of the CSAW Study is the responsibility of the trial statistician. A full statistical analysis plan will be written by the trial statistician and agreed upon by the independent Data Monitoring Committee (DMC) before any analyses are undertaken.

Baseline data will be compared to determine whether there are any clinically important differences between treatment groups that have occurred by chance. It is anticipated that STATA statistical software (StataCorp, College Station, TX, USA), or another validated statistical software package such as SAS (SAS Institute, Cary, NC, USA) or R (versions will be recorded in the Statistical Report), will be used in the analysis.

All statistical testing will be performed at the two-sided 5% significance level, and 95% confidence intervals will be presented where appropriate. For all analyses, the appropriate model assumptions will be verified, and alternative methods will be used if more appropriate.

Prior to any analysis, any missing data pattern will be investigated and reasons for missing data obtained and summarised where possible. The primary analysis will be conducted on the modified intention-to-treat analysis, which includes all participants with nonmissing outcome data, unless there is clear evidence that its underlying assumption is inappropriate. Sensitivity analysis will be performed to assess the robustness of the results by imputing missing data using multiple imputation under both missing at random and missing not at random assumptions.

##### Frequency of analysis

A DMC will be set up to independently review the data on safety, protocol adherence and recruitment. Interim reports will be presented to the DMC in strict confidence at a minimum of yearly intervals. As no formal stopping rules have been specified for this trial, no formal interim analyses are planned, and hence no statistical testing will take place until the final analysis. The final analysis will take place after all participants have completed their follow-up and sufficient time has been allowed for data entry and validation.

##### Primary endpoint analysis

The primary outcome measure is the OSS measured at 6 months postrandomisation. The treatment groups are ASAD, AO and AMSR.

Multivariate linear regression analysis (analysis of covariance (ANCOVA)) will be used to examine the effect of the randomised intervention on the OSS at 6 months postrandomisation using three separate two-way comparisons (that is, ASAD vs. AMSR, ASAD vs. AO, and AO vs. AMSR). The model will be adjusted for (continuous) baseline OSS, sex, age and other relevant patient characteristics if appropriate. The minimisation factors (excluding centre) which are of clinical importance will be adjusted for in the model, regardless of statistical significance. Transformation of skewed variables will be considered, as will inclusion of polynomial terms if appropriate.

In additional secondary analyses, we will investigate the effect on the treatment estimates when long waiting times before surgery are taken into account. Participants with long waiting times before surgery may not yet have reached their optimal point of recovery when assessed at 6 months postrandomisation, and their data may underestimate the true treatment effect of their intervention. Analyses will include substituting the baseline and 6 months postrandomisation data for data collected at the presurgery and six months postsurgery assessments, respectively, for participants with a delay longer than 16 weeks before surgery. For participants with a long delay before surgery, the 6 months postsurgery assessments will coincide approximately with their 12 months postrandomisation assessment.

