**Methods/Design:**

The trial is a three-group, parallel design, pragmatic, randomised controlled study. The intervention content for each group (ASAD, active monitoring with specialist reassessment (AMSR) and investigational shoulder arthroscopy only (AO)) enables assessment of (1) the efficacy of the surgery against no surgery; (2) the need for a specific component of the surgery—namely, removal of the bony spur; and (3) quantification of the placebo effect. Concealed allocation was performed using a 1:1:1 randomisation ratio and using age, sex, baseline Oxford Shoulder Score (OSS) and centre as minimisation criteria. The primary outcome measure is the OSS at 6 months post randomisation. A total of 300 patients recruited over 24 months from a minimum of 14 UK shoulder units over 24 months were required to detect a difference of 4.5 points on the OSS (standard deviation, 9) with 90% power and to allow for 15% loss to follow-up. Secondary outcomes include cost-effectiveness, pain, complications and patient satisfaction. A substantial qualitative research component is included. The primary analysis will be conducted on the modified intention-to-treat analysis. Sensitivity analysis will be used to assess the robustness of the results with regard to the underlying assumptions about missing data using multiple imputation.

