### Number of centres

Participants will be recruited at NHS hospitals throughout the United Kingdom. An initial minimal set of centres (n = 14) is planned; however, if recruitment rate indicates the need, the number of recruiting centres will be increased accordingly. The initial centres involved in the CSAW Study are known to the study team from previous collaboration in the United Kingdom Rotator Cuff Trial (UKUFF study; ISRCTN97804283). Their contribution and recruitment rates were reviewed in preparation for the CSAW Study protocol.

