#### Randomisation

After written informed consent is obtained and patient eligibility is confirmed, and immediately after the baseline appointment, patients will be randomised into the study by site staff authorised to perform telephone randomisations. Randomisations will be performed centrally by the Oxford Clinical Trials Research Unit within office hours (8 am to 5 pm), Mondays to Fridays, excluding public and/or bank holidays. The following information will be required at the randomisation call: participant details, research site details, name of caller, name of treating consultant, confirmation of eligibility, confirmation of written informed consent and its date, and stratification factors (see below).

Patients will be allocated a study number and will be randomised on a 1:1:1 basis to receive one of the three treatment options: ASAD surgery, AO or AMSR.

Randomisation will be performed using an automated, computer-generated minimisation system to ensure that treatment groups are well balanced for the following patient characteristics, the details of which will be required for the randomisation:Age (<40, 40 to 55 or 56+ years)SexBaseline OSS (<19, 19 to 26, 27 to 33 or 34+)Centre

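### Centre is a minimisation factor but is left out of the primary ANCOVA by rule, so reported standard errors are slightly too large if centres differ (minor, conservative)

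*Protocol article*

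**What the plan says.** The abstract of the protocol article describes allocation "using age, sex, baseline Oxford Shoulder Score (OSS) and centre as minimisation criteria". The Randomisation section repeats the four factors and describes an "automated, computer-generated minimisation system to ensure that treatment groups are well balanced" on them.

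For the primary outcome, OSS at 6 months, the section Primary endpoint analysis plans an ANCOVA for each of three two-way comparisons: "The model will be adjusted for (continuous) baseline OSS, sex, age and other relevant patient characteristics if appropriate". The next sentence sets the rule for the allocation factors: "The minimisation factors (excluding centre) which are of clinical importance will be adjusted for in the model, regardless of statistical significance".

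No other section puts centre back into the primary model. The multilevel model under Secondary endpoint analyses nests repeated OSS measurements within participants, not participants within centres. The General considerations allow other methods if model assumptions fail, but do not mention centre.

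On scale, the section Number of centres says: "An initial minimal set of centres (n = 14) is planned", with more to be added if recruitment requires it.

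**The concern.** Balancing the arms within centre removes most between-centre variation from the treatment contrast. A model without centre still counts that variation as residual noise. If centres differ in outcome, the reported standard error then exceeds the true one. The protocol follows the opposite principle for the other three allocation factors, which stay in the model whatever their p-values.

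The document makes some centre variation plausible. Diagnosis follows each site's own route (Inclusion criteria), recruitment arrangements differ by site (Recruitment organisation), and surgeons manage their own waiting lists (Study assessments). Primary endpoint analysis itself expects long waits to affect the 6-month result.

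A conservative error is not entirely harmless here. Under Concept, failure to reject is read as informative: for ASAD against AMSR it would put the continued use of surgery in question, and for ASAD against AO it may indicate that bone removal is not needed. Intervals that are too wide lean, slightly, towards those readings.

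**Working it through.** **Inputs from the Sample size calculation section:** "90% power to detect a difference in OSS of 4.5 (SD 9.0"), "with a two-sided 5% level of significance", and "a sample size of 85 participants is needed in each group". Dropout allowance 15%.

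**Assumed, because the document gives no figure:** a residual centre ICC, ρ, after adjustment for baseline OSS, age and sex, set at 0.02, 0.05 and 0.10. Also assumed: SD 9.0 is the total residual SD, the treatment effect is the same in every centre, and the arms are near-completely balanced within centre.

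**Step 1. The plan's own figure.** n = 2(z₀.₉₇₅ + z₀.₉₀)²(SD/Δ)² = 2 × (1.960 + 1.282)² × (9.0/4.5)² = 2 × 10.51 × 4 = 84.1, so 85 per group; 85/0.85 = 100. The stated figures reproduce. (The noncentral t gives 86, with power 0.8999 at 85; the difference is immaterial.)

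**Step 2. Standard error reported with centre omitted.** 9.0 × √(2/85) = 1.381, giving a 95% half-width of 1.96 × 1.381 = 2.71 points.

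**Step 3. True standard error when arms are balanced within centre.** 1.381 × √(1 − ρ). The reported value is too large by the factor 1/√(1 − ρ).

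**Step 4. Consequences.**
- True type I error, centre omitted: 2[1 − Φ(1.96/√(1 − ρ))]
- Power, centre omitted: Φ((4.5 − 1.96 × 1.381)/(1.381√(1 − ρ)))
- Power, centre in the model: Φ(4.5/(1.381√(1 − ρ)) − 1.96)

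For ρ = 0.05, the true SE is 1.346 and the ratio 1.026. Power with centre omitted is Φ(1.333) = 90.9%, and with centre Φ(1.384) = 91.7%.

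| Assumed ρ | True SE | Reported SE too large by | True alpha | Power, centre omitted | Power, centre in model | Half-width, omitted v in model |
|---|---|---|---|---|---|---|
| 0.02 | 1.367 | 1.0% | 0.048 | 90.54% | 90.87% | 2.71 v 2.68 (0.03) |
| 0.05 | 1.346 | 2.6% | 0.044 | 90.88% | 91.69% | 2.71 v 2.64 (0.07) |
| 0.10 | 1.310 | 5.4% | 0.039 | 91.46% | 93.00% | 2.71 v 2.57 (0.14) |

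Power forgone is 0.33, 0.81 and 1.54 percentage points. At ρ = 0 the two analyses agree (power 90.3%).

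**Step 5. Form of adjustment.** Minimisation on all four factors was simulated with 255 participants analysed over three arms.
- *Fixed centre effects (1,500 runs per setting), mean SE, omitted v adjusted.* 14 centres: 1.380 v 1.380 at ρ = 0.02; about 1.38 v 1.36 at 0.05; 1.37 v 1.32 at 0.10. 30 centres at ρ = 0.05: 1.376 v 1.393, so adjustment made it worse.
- *Random intercept (3,000 runs per setting), mean SE, omitted v adjusted.* 14 centres: 1.378 v 1.348 at ρ = 0.05; 1.372 v 1.312 at 0.10. 30 centres: 1.379 v 1.350 and 1.377 v 1.319. At ρ = 0: 1.378 v 1.374 (14 centres) and 1.379 v 1.373 (30). Type I error was 0.045 to 0.055, with simulation error about 0.004.

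With 14 centres the random-intercept ratios are 1.378/1.348 = 1.022 and 1.372/1.312 = 1.046, a little below the closed-form 1.026 and 1.054. Balance under four-factor minimisation is incomplete, so the table is best read as an upper end for each ρ. Rejection rates in the 1,500-run simulation are too noisy to settle the alpha column: the standard error is √(0.05 × 0.95/1,500) = 0.006, and at ρ = 0.10 with 14 centres and centre omitted the rate was 0.051.

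**The case against.** The strongest reply is that this hardly matters. Even at ρ = 0.10 the half-width changes by 0.14 points against a 4.5-point target, power without centre stays above the planned 90%, and the error is on the safe side. The relevant ICC is the one left after baseline OSS, age and sex, which already remove part of any case-mix difference between centres, so 0.10 is the high end of an assumed range. All of this stands, and it is why the point is minor.

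A second reply is that adjusting for centre can backfire. The section Recruitment rate and access to the National Health Service implies 21 to 22 patients per centre, about 7 per arm, and fewer as centres are added. This stands against fixed effects, as Step 5 shows, but not against a random intercept.

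Third, General considerations promises a full analysis plan and allows alternative methods. That limits the consequence but does not cancel an explicit exclusion.

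Fourth, surgery is delivered by different surgeons, so the treatment effect itself may vary by centre. That could push the standard error the other way, and a random intercept does not model it. This is a fair limit on the calculation, which assumes a common effect.

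A reader might also infer that the secondary analyses exclude centre. They do not say so: they refer to relevant minimisation factors without the exclusion.

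**Conclusion.** The mismatch between allocation and analysis is real, stated as a rule and unexplained. If centres differ in adjusted mean OSS, reported standard errors are about 1.0% to 5.4% too large for an assumed residual ICC of 0.02 to 0.10, with true alpha 0.048 to 0.039 and roughly 0.3 to 1.5 percentage points of power forgone. These figures rest on an ICC that the document does not give, on near-complete balance within centre and on a common treatment effect. If centres do not differ, nothing is lost.

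Three stronger readings are not supported. The primary tests are not anti-conservative and the estimate is not biased, because the error runs towards caution. The precision gained by balancing on centre is not thrown away: the estimator already benefits from it, and what is missing is mainly its recognition in the reported standard error. The trial is not left underpowered by this choice, since power with centre omitted stays at or above about 90% throughout.

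Severity: minor.

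**What to change.** In Primary endpoint analysis, strike the bracketed words that leave centre out, and state that each of the three two-way comparisons includes a random intercept for centre alongside continuous baseline OSS, age and sex. Do not use fixed centre effects, which can cancel the gain when centres are many and small. The planned two-way structure can stay; whether to fit one model to all three arms is a separate question that this argument does not settle.

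The cost is one sentence and one variance component. Centre is already recorded at the randomisation call, so no data need to be added. If centres do not differ, there is essentially no gain and essentially no loss.

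If there is a reason to keep centre out, the lesser alternative is to state it and prespecify a sensitivity analysis with the random intercept.
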